### Costing

To inform the social impact of fistula management and future cost-effectiveness assessment, we will summarize fistula management cost data descriptively for cup, cup+, and usual non-surgical methods; measurement of central tendency will be generated. We will compare fistula management costs by use domains between cup, cup+, and usual non-surgical methods using chi-square tests, Kruskal-Wallis H tests, and Nemenyi post-hoc tests.

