**Table 1 Tab1:**
[figure not shown]
Description of the cup and cup + Intervention models

Cost is an important implementation outcome for this and any fistula management intervention. Although qualitative studies have suggested women devote significant time and effort to non-surgical fistula management, [14, 26, 44, 45] no rigorous quantification of material and opportunity costs exists. As such, the economic burden of fistula is not well understood, which limits valid estimation of the benefits of fistula interventions. Micro-costing of non-surgical management is needed to quantify the burden of managing fistula urine leakage to comprehensively characterize the social and economic impact of any fistula management intervention. Cost-effectiveness of fistula surgery has been previously evaluated in Uganda, showing that for a hypothetical 20-year-old woman with fistula, surgery was estimated to decrease the lifetime disability burden from 8.53 DALYs to 1.51 DALYs, yielding a cost of $54 per DALY averted [46]. However, cost comparisons and cost-effectiveness analysis have yet to be conducted between methods of self-management of fistula. Various aspects contribute to financial and economic cost of fistula management; 47] valved menstrual cups that would meet the needs identified in our prior research are now available (cost of $4.50 per unit) and tubings with leg bags are readily available (combined cost of $6.10 per unit).

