## Methods

### Study design

This hybrid type I randomized crossover phase III clinical trial and nested qualitative [59] study employing a concurrent mixed-methods approach (Fig. 1) [60] seeks to longitudinally quantify the effectiveness and comparative effectiveness of the cup and cup + to manage vesicovaginal fistula urinary incontinence (Aim 1) among up to 100 women in Ghana and Kenya who have not yet accessed treatment or have failed surgical repair, examine acceptability of the cup and cup+ (Aim 2), and estimate the material and opportunity costs of non-surgical fistula management (Aim 3).

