Cross-over trial designs provide greater efficiency than parallel designs due to within-subject treatment comparisons where each subject serves as their own control, resulting in lower sample size requirements for statistical power. Our sample size of up to 100 participants (400 observations) is calculated to assess: (1) a ≥ 65% reduction at six hours in observed urinary leakage, and (2) a mean 40% quality of life difference at three months between the cup and cup+ (measure range 0-100; Supplementary Figures). We expect > 80% retention over three months study follow-up based on our research with 12-months follow-up with 98% retention with this target population in Uganda^63^ and 3-months follow-up in Ghana with 84% retention, [64, 65] and have inflated our target sample size conservatively.

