Cost data will be captured from all trial participants. Participants will self-report estimates of usual time and resources spent managing incontinence and, within the facility-based procedures, time spent managing incontinence over the 24 h periods assigned to leaking freely, using cup, and using cup+. During community-based follow up, these individuals will be surveyed with the same questions monthly through three months [78, 79]. We will micro-cost fistula-related resources using published prices [80]. Community-administered surveys will include measures of cost for supplies related to fistula management and productivity lost; we will supplement the TM data with data on opportunity costs collected within our acceptability assessment (Aim 2). Clinic treatment cost (e.g., human resources and provider time effort) will be collected from facility managers. In addition, average sales and wholesale prices of supplies will be combined with utilization patterns captured during TM to calculate fistula management cost and to supplement participant-reported costs. The three data sources will comprehensively capture the range of fistula management costs. To minimize discrepancy, we will provide detailed activity categories in our survey (e.g., inserting/removing cup, washing, etc.). To maximize rigor, participants will be trained on 24-hour activity reporting during their time at the facility.

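### The tests named for comparing costs are rank-based or chi-square and do not address the mean cost difference that the stated cost-effectiveness purpose needs

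*Protocol article*

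**What the plan says.** The Study design section sets the third aim as to "estimate the material and opportunity costs of non-surgical fistula management (Aim 3"), which is an estimation aim.

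The Costing study section says "Cost data will be captured from all trial participants". Women report their usual time and resources. In the clinic they also report "time spent managing incontinence over the 24 h periods assigned to leaking freely, using cup, and using cup"+. The same questions are then asked monthly at home. Under Community-based procedures, each woman is individually randomized to take home one device, the cup or the cup+.

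The Costing paragraph under Data analysis is the only text on how costs will be analysed. Its first sentence gives the purpose, "To inform the social impact of fistula management and future cost-effectiveness assessment", and plans a descriptive summary in which "measurement of central tendency will be generated". It does not say whether that means the mean or the median. Its second sentence compares costs by domain of use "between cup, cup+, and usual non-surgical methods using chi-square tests, Kruskal-Wallis H tests, and Nemenyi post-hoc tests". No model, test or interval for a mean or total cost is stated.

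**The concern.** Kruskal-Wallis and Nemenyi compare rank positions, and chi-square compares category frequencies. A cost-effectiveness assessment uses expected cost: mean cost times the number of women gives the total burden, and the mean difference is the numerator of any cost-per-outcome ratio. Mean costs by domain also add up to mean total cost, which rank results by domain do not.

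When distributions differ only by a shift or a common scaling, ranks and means point the same way. When their shapes differ, they need not. Different shapes are plausible here. The devices have fixed prices (the Background gives the cup a "cost of $4.50 per unit" and the tubing with leg bag $6.10), while usual management is recurrent spending and time on absorbent materials and washing. Aim 3 could then report a significant cost ordering that the mean costs do not share, with no stated inference on the quantity the later work needs.

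**Working it through.** The article gives no mean, SD, sample size or alpha for costs, so there is no figure of its own to reproduce. The check is an illustration of the named procedure.

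**Inputs from the article**
- Up to 100 women, and "We expect > 80% retention over three months study follow-up" (sample size section), so about 80 women.
- One device per woman at home. Assuming an even split, 80 / 2 = 40 cup and 40 cup+ reports, against 80 usual-management reports.

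**Assumed inputs**
- Log-normal costs, independent reports, alpha 0.05.
- More skewed option: median 7.5, log-SD 0.91. Less skewed option: median 10, log-SD 0.5.

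**Means.** Mean = median × exp(log-SD² / 2).
- 7.5 × exp(0.91² / 2) = 11.35
- 10 × exp(0.5² / 2) = 11.33

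The means are equal for practical purposes.

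**Approximate size by hand, device more skewed**
- P(device cost < usual cost) = Φ(ln(10 / 7.5) / √(0.91² + 0.5²)) = 0.609.
- Expected mean rank, cup: 1 + 39 × 0.5 + 40 × 0.5 + 80 × 0.391 = 71.8.
- Expected mean rank, usual: 1 + 79 × 0.5 + 80 × 0.609 = 89.2. The difference is about 17.5.
- Null standard error, N = 160: √[160 × 161 / 12 × (1/40 + 1/80)] = √80.5 = 8.97.
- Nemenyi threshold for three groups: (3.314 / √2) × 8.97 = 2.343 × 8.97 = 21.0.
- Chance of crossing it, using the null standard error: 1 − Φ((21.0 − 17.5) / 8.97) ≈ 0.35.

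**Simulation of Kruskal-Wallis at 0.05 followed by Nemenyi, groups of 40/40/80**

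| Setting | Cup called cheaper | Cup called dearer |
|---|---|---|
| Equal means, device more skewed | 34% to 36% over repeated runs | 0% |
| Equal means, usual management more skewed | 0% | about 33% |
| Device median 7.0, log-SD 1.05 (mean 12.15, 7% higher), usual as above | about 43% | 0% |
| Equal means, equal shapes | about 1% | about 1% |

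With equal shapes the overall Kruskal-Wallis rejection rate is about 5%.

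**Sensitivity to repeated measures.** Each woman contributes to more than one option, so the reports are not independent. With three groups of 80 and within-woman correlation 0.5, the equal-shape rejection rate falls to about 0.3%. With equal means and log-SDs of 1.2 (devices) and 0.8 (usual), the cup is still called cheaper in about 53%, against 51% with independent groups. Correlation lowers the error when shapes are equal but does not remove the disagreement when they differ.

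**The case against.** Several points on the other side have force.

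- **The purpose phrase opens the descriptive sentence, not the testing sentence, and central tendency may include means.** This stands. A reader might infer that the trial will produce no mean costs at all, and the text does not support that. What is not stated is any inference on the difference in means.
- **No rule for declaring a device cheaper exists.** This stands. A reader might infer that the plan will declare a device cheaper when its mean cost is equal or higher. The article sets no such rule, and it places cost-effectiveness analysis in future work.
- **The direction of skew is not known.** This stands. The article calls the cup durable and low-cost, so usual spending could well be the more variable, and the disagreement would then count against the device.
- **Ranks answer a legitimate question.** In the first scenario the device median is 25% lower and a random device cost lies below a random usual cost 61% of the time, so the test detects a real difference. That suits a description of typical user burden, but not the input to a cost-effectiveness assessment.
- **A condensed article leaves detail to the analysis plan.** This is partly right. Which summary and which interval could be settled there. But the article does name the comparison methods, and a plan consistent with it would keep them. The general remark that transformations will be considered does not help, because a log scale targets the geometric mean.

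**Conclusion.** The point holds as a mismatch between the named comparisons and their stated use. The only tests named for costs do not address mean cost, and their result can differ from the mean comparison in either direction when cost distributions differ in shape.

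Under the assumptions above, the chance of a significant cup-versus-usual difference with equal means is about one third, in whichever direction the skew dictates. With equal shapes it is nominal, or lower when reports are correlated. These sizes rest on assumed log-normal shapes and an assumed even split of about 80 retained women; the mismatch itself does not.

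The weight is modest: costing is Aim 3, no decision hangs on the tests, and descriptive means may be reported. It is an inexpensive improvement, not a threat to the trial's main conclusions.

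**What to change.** Rewrite the Costing paragraph so that the main Aim 3 comparison is the arithmetic mean cost, and mean time, per woman under each option, with mean differences and bootstrap 95% confidence intervals that resample women. Resampling women also respects the repeated reports.

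- Use within-woman differences for the clinic conditions (leaking freely, cup, cup+) and for a device against the same woman's usual management.
- Use between-woman differences for home cup versus home cup+, because each woman takes home only one device.
- Keep the rank and chi-square tests, if wanted, as descriptive support.

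The change needs no new data, only wording and a few lines of code. The downside is wider intervals when a few women have very high costs.

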### Costing study

Using time motion study (TM)^77^ and micro-costing methods, we will longitudinally survey all trial participants (*n* = up to 100) while in the facility and during community-based follow-up on fistula management practices to estimate direct costs (medical and nonmedical) and indirect costs (productivity) from the patient perspective. We will compare fistula management costs between cup, cup+, and usual non-surgical methods to inform the social impact of fistula management and future cost-effectiveness assessment. While it is often recommended that time motion is conducted with an external observer, [77] the sensitivity and stigma surrounding non-surgical fistula management makes the employment of an external observer of personal hygiene behavior inappropriate. Nevertheless, it is critical to capture individual indirect cost of non-surgical fistula management and how the cost may vary across interventions thus we rely on participant self-report of non-surgical fistula management in the community. Potential for bias will be minimized through use of standard questions focused on 24-hr recall. During community-based follow-up by the research assistants, multiple assessment points will allow us to observe change over time as well as understand the influence of community-level factors (e.g., distance to latrine, accessibility of water) on non-surgical management.

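### The costing analysis names independent-group tests for costs and times that come largely from the same women, so its p-values will not have their nominal level

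*Protocol article*

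**What the plan says.** The Costing paragraph under Data analysis first promises descriptive summaries. It then names the comparison, "We will compare fistula management costs by use domains between cup, cup+, and usual non-surgical methods", and the methods: "using chi-square tests, Kruskal-Wallis H tests, and Nemenyi post-hoc tests". It mentions no pairing, participant effect or clustering.

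The Costing study section says where the data come from:
- **Source.** "Cost data will be captured from all trial participants".
- **Usual management.** "Participants will self-report estimates of usual time and resources spent managing incontinence".
- **Clinic phase.** The same women report "time spent managing incontinence over the 24 h periods assigned to leaking freely, using cup, and using cup" (the last of these is cup+).
- **Home phase.** "these individuals will be surveyed with the same questions monthly through three months".

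The Randomization section describes the clinic phase as a crossover in which women serve as their own controls. It has two sequences: leaking freely occurs twice in group 1 and cup occurs twice in group 2. Under Community-based procedures, each woman is then individually randomized to one device, cup or cup+, for up to three months.

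**The concern.** The Kruskal-Wallis and chi-square tests take their reference distribution from groups made up of different people. Most of the costing data are not of that kind. A woman with a large fistula, or far from water or a latrine, is likely to spend more time and money under every condition, so her values are correlated.

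Ignoring this can do harm in two ways. Where each woman gives one value per condition, stable differences between women are left in the error term. The test becomes too conservative, and the efficiency the crossover was chosen for is lost. Where several monthly reports from one woman are counted as separate people, the information on cup versus cup+ is overstated and false positives rise.

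The article handles the same structure correctly elsewhere: six-hour leakage gets a linear mixed model with subject-specific random intercepts, and short-term acceptability gets paired tests. The costing paragraph departs from this without giving a reason. At stake are the inferential results of Aim 3, which are meant to inform later cost-effectiveness work.

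**Working it through.** **Is there a figure to reproduce?** No. The article gives no power, alpha or sample size for cost. Its one related sum, 100 women × 4 clinic observations = 400, is consistent.

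**Inputs from the document.** Up to 100 women; three conditions compared; three monthly home surveys; each woman on one device at home; more than 80% retention expected (80 of 100 used for the home phase, taken as 40 per device).

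**Assumptions not in the document.** Within-woman correlation ρ of 0.3, 0.5 and 0.7, equal between all pairs of reports; costs normal on the log scale; a shift of 0.25 SD in one condition; nominal two-sided alpha of 5%.

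**Step 1: clinic phase, size.** The difference between two conditions in the same woman has variance 2σ²(1−ρ), whereas an independent-group test supposes 2σ². With three conditions, the Kruskal-Wallis statistic under the null behaves approximately like (1−ρ) times a chi-square on 2 degrees of freedom, with 5% cut-off 5.99. True size ≈ exp{−5.99 / [2(1−ρ)]}:
- ρ = 0: exp(−2.995) = 5.0%
- ρ = 0.3: exp(−4.28) = 1.4%
- ρ = 0.5: exp(−5.99) = 0.25%
- ρ = 0.7: exp(−9.98) = 0.005%

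Simulation agrees: about 1%, 0.2% and 0% at ρ = 0.3, 0.5 and 0.7. The Friedman test stays at 5.1-5.7% throughout. The chi-square test for a binary item falls to 2.2%, 1.2% and 0.2%, while Cochran's Q stays at 4.4-5.2%.

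**Step 2: clinic phase, power (simulated, n = 100, one value per woman per condition).**

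| ρ | Kruskal-Wallis | Friedman |
|---|---|---|
| 0.3 | about 37% | about 46% |
| 0.5 | about 31% | about 60% |
| 0.7 | about 25% | about 83% |

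At ρ = 0 there is no loss. Under a slightly different alternative (shifts of 0, −0.15 and −0.30 SD), Kruskal-Wallis then does rather better than Friedman, 44% against 35%.

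**Step 3: home phase, one visit per woman (n = 80).** Usual versus device is within woman, so its variance is multiplied by (1−ρ). Cup versus cup+ is between women, and its variance is right. Simulated Kruskal-Wallis size is 3.1%, 2.2% and 2.1% at ρ = 0.3, 0.5 and 0.7, which is still conservative.

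**Step 4: home phase, three monthly reports pooled as independent.** Each arm then appears to hold 40 × 3 = 120 independent reports. For cup versus cup+ the true variance exceeds the supposed one by 1 + (3−1)ρ = 1.6, 2.0 and 2.4. Usual versus device is still too conservative, by the factor (1−ρ), but the inflation dominates. Simulated size is 7.6%, 9.9% and 12.3%.

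**The case against.** Several points on the other side are fair.

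- **Not all comparisons are paired.** A reader might infer that costs under cup, cup+ and usual management always come from the same women. The individual home randomization rules that out: cup versus cup+ at home compares different women, and at a single visit an independent-group test is legitimate for it. The home surveys are also where supply costs and lost productivity are asked. This narrows the point but does not remove it, because usual versus device at home stays within woman.
- **Clinic data are mainly about time.** A reader might infer that resources are reported for every clinic condition. The Costing study text names only time for the 24 h periods and attaches resources to usual management. Table 2 does list a combined practices, time and costs item at 24 h, so resources may be collected, but the text does not say so. Usual methods and leaking freely in the clinic are also reported separately and need not be the same condition.
- **The direction is not fixed.** It is tempting to say that real differences will be reported as non-significant. That holds for one value per woman per condition and fails if monthly reports are pooled.
- **The power loss is conditional.** It is modest at a correlation of 0.3 and absent at 0, and the document gives no correlation.
- **Nemenyi is not itself the fault.** It also exists in a form that follows Friedman.
- **The stakes are limited.** Costing is Aim 3, description comes first, and no sample size rests on it.

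Nor can the matter be left to an unseen analysis plan: the article itself names the tests, and they do not fit the data it describes.

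**Conclusion.** The point holds in limited form. For the clinic comparisons, and for usual management versus either device at home, the named chi-square and Kruskal-Wallis tests do not match the data, and their p-values will not have the stated level. That conclusion requires only some positive within-woman correlation, which the own-control rationale of the crossover presupposes.

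The size of the problem rests on the assumptions listed in the working. The error runs from strongly conservative, with roughly half the power lost at a correlation of 0.5 (31% against 60%), to a false-positive rate of about 8-12% if monthly reports are pooled. The article does not say which arrangement will be used, so neither direction can be asserted as what will happen.

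This should be corrected, but it does not threaten the trial's main result, because six-hour leakage is already modelled with a random intercept for each woman.

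**What to change.** Replace the named tests with a mixed or GEE model for cost and time, for example with a log link or gamma errors, reporting cost ratios or mean differences with confidence intervals:

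- **Clinic phase:** a participant effect with condition and period terms. This also handles the fourth period, in which leaking freely or cup is repeated.
- **Home phase:** a participant effect with visit terms, usual cost at baseline as a repeated measure or covariate, and cup versus cup+ as a between-arm contrast.
- **Categorical items:** the corresponding binary model.

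If a rank test is kept for the clinic phase, first reduce the data to one value per woman per condition, then use Friedman with its Nemenyi post-hoc test. Friedman cannot be applied directly to four periods with one condition repeated, and it ignores period.

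The cost is a change of analysis wording. No new data, visits or participants are needed, and the team already plans mixed models for leakage.

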### Qualitative

Interviews will be transcribed and coded to address research questions and open-coded for additional themes [85, 86]. We will use the framework analysis method to provide a systematic model for managing and integrating the quantitative and qualitative data on user acceptability, qualitative data on implementer acceptability, and facilitators and barriers to implementation [87]. We will compare acceptability constructs within and between users and implementers. Strategies for rigor include seeking and incorporating feedback from Community Advisory Board members and using an audit trail [88]. Analysis of qualitative outcomes of acceptability will follow a two-stage systematic process and interviewers who translated/transcribed will help the binational research team with coding. First stage: data coding and classification by reviewing transcripts for conceptual categories. Two types of codes: deductive and emergent. First, deductive codes that represent expected influences will be applied, taken from existing literature and interview guide oriented by the CFIR [75, 76, 89]. This will include examination of acceptability by difference between those recruited from northern or southern regions, different cultural groups, and rural/urban to examine different concerns across settings. For stakeholder interviews recruiting men and women, we will examine acceptability differences by gender/sex. Next, emergent codes will represent themes not expected by the researchers. A codebook will include detailed code description, code application criteria, and examples. Data will be analyzed by different dimensions and commonalities of themes, patterns, and linkages, and by participant characteristics. Exploratory analyses by user characteristics (e.g., fistula size, incontinence severity, or physical activity intensity) may help identify optimal users for each of the device modifications that could be examined in future research. Integration of quantitative and qualitative data from quantitative and qualitative findings via joint analysis [62] will also contextualize effectiveness outcomes through our sequential explanatory approach.

